#### Delivery of implementation strategy to clusters

The delivery of the implementation strategy to the 12 clusters will be assessed using standardized attendance lists (data source A). The individuals (name, profession and function) participating in the steering group meetings and additional in-service training will be documented (3a, b). Moreover, nonconformities to the meeting curricula of the steering group and additional in-service training will be documented. Deviations will be recorded in relation to the participants, durations, didactic methods and contents of the training units (data source C).

#### Response of individuals to implementation strategy

The attitudes of individuals toward the implementation strategy will be assessed first using standardized evaluation sheets that will be distributed to the participants at the steering group meeting (2) and the additional in-service training (3a, b) at the end of each session (data source F). Moreover, four semi-structured telephone interviews [37] with the head nurse of each nursing team (data source G) will be carried out to gain insight into the overall attitudes of the target populations toward the implementation strategy. Finally, semi-structured group interviews [38] will be conducted with all of the moderators, the steering group and all 24 nursing teams at the end of the intervention phase (data sources H, I and J).

#### Response of cluster to implementation strategy

For the response of the clusters toward the implementation strategy, four semi-structured telephone interviews [37] will be conducted with the head nurses of each participating nursing ward during the intervention phase. The head nurse should take part in the steering group meeting (data source G). Therefore, the interviews with the head nurse will aim to assess whether the steering group has supported the implementation process of the dementia-specific case conferences and assisted the nursing teams in implementing them in their daily routines. Finally, semi-structured group interviews [38] will be conducted with the steering group, the moderators and the nursing teams (core teams) at the end of the intervention phase to evaluate the overall response of the cluster to the implementation strategy (data sources H, I and J).

#### Recruitment and reach of individuals with implementation strategy

The recruitment and reach of individuals with the implementation strategy will be explored using semi-structured group interviews [38] with the steering groups (data sources J). The interviews will address the criteria that clusters have used to allocate the members of the steering group and the moderators. Moreover, standardized questionnaires will be used to evaluate who in the target population actually took part in the steering group meetings and additional in-service trainings (3a, b) (data source F).

All semi-structured telephone and group interviews, as well as the audiotapes of the dementia-specific case conferences, will be transcribed verbatim by a professional translation agency and subsequently proofread by one member of the research team prior to data analysis. For the transcription of the interviews, the method of Kuckartz [40] will be used.

### Data analysis

The FallDem study will be evaluated using a mixed-method design comprising qualitative and quantitative data, which will complement each other, providing a more comprehensive picture of the different concepts under investigation [41]. Guest [42] has noted that consideration of the point of interface (the integration of qualitative and quantitative data) leads to the perspective that ‘the timing and the purpose of data integration’ are the most important:

‘The timing of integration is critically important because it not only conveys when data sets are used with respect to one another but also whether the data sets depend on each other. The purpose of integration denotes the reason for connecting or mixing data sets at each stage of the research process’ ([42] page 147).

Bazeley and Kemp have argued that there must be ‘interdependence of component approaches during the analytic writing process (…)’ ([43] page 69). Simply preparing final conclusions on the basis of different datasets does not mean that the methods have been integrated. Therefore, integration must occur before conclusions are drawn, the results of which will represent ‘something that would not have been available without that integration’ ([43] page 69).

In this study, data integration will take place on two levels. First, data within the same domain of the process evaluation will be combined to obtain a comprehensive picture of each domain and across domains. For this purpose, integrated analysis will be performed using a DNA double helix method, which compromises sense and antisense strands [44]. Expecting divergent results (within and across domains), this strategy will allow for the determination of concordant findings (the sense strand of the analysis; based on previous studies and expected results) and the consideration of antisense or dissonant findings as counterpoints (the findings of the current FallDem study):

‘The divergence of findings can then be used as a promoter (and) can continue in a series of iterations. (…) Thus, reconciliation is sought by undertaking analysis that facilitates a continuous dialogue or exchange of multiple data to understand the phenomena of interest’ ([43] page 67f).

Second, data from the three domains, including the delivery of the intervention to the cluster, response of individuals to the intervention and response of cluster to the intervention, will be integrated in the statistical analysis of the FallDem effectiveness study through blendin*g*[43], meaning that a new variable (time combined with the success of the implementation) will be integrated in the generalized linear mixed-effects model [13]. To achieve this aim, the integration of the data will also be performed in a transformative manner using quantized qualitative coding (the success of the implementation), which can be analyzed in relation to each cluster (also see defining the delayed treatment effect) (Tables 6 and 7).

**Table 6 Tab6:** **Data analysis of domains of intervention**

Domain	Research question	Data source		Theoretical basis	Method of data analysis	Method of data integration
Delivery of clusters (intervention)	1. Was the intervention delivered as intended for each nursing home (cluster)?	A	attendance lists of in-service training in performing case conferences (I), training on the job (II) and case conferences without support (III)	▪ Case conference model (key characteristics)	▪ Descriptive statistics [45]	▪ DNA double helix
						▪ Blending
						▪ Transformation
		B	standardized protocols of dementia-specific case conferences	▪ Case conference model (process structure and key characteristics)	▪ Documentary analysis [46]	
		C	written documentation of in-service training in performing case conferences (I)and training on the job (II) (deviation from curriculum)	▪ Curriculum (in-service training in performing case conferences (I) and on-the-job training (II))	▪ Documentary analysis [46]	
Response and reach of individuals (intervention)	2. Which learning processes of the target population took place in response to the intervention?	D	audiotapes of case conferences of four nursing teams (n =24/6 per team); 2 teams using WELCOME-NEO and 2 teams performing WELCOME-IdA	▪ Act for teams, Kasseler competence inventory [47]	▪ Documentary method [48]	-
	3. What is the attitude of the target population toward the intervention?	E	standardized questionnaire to assess attitudes towards case conferences	▪ Adoption model [49]	▪ Descriptive statistics [45]	▪ DNA double helix
						▪ Blending
		F	standardized questionnaire to evaluate in-service training in performing case conferences (I) and training on the job (II)	▪ Curriculum (in-service training in performing case conferences (I) and on-the-job training (II)	▪ Descriptive statistics [45]	▪ Transformation
		G	semi-structured telephone interviews to evaluate case conferences (n = 96/6 per nursing team)	▪ Adoption model [49]	▪ Content analysis [50]	
		H	semi-structured group interviews to evaluate intervention (n = 12)	▪ Adoption model [49]	▪ Content analysis [50]	
		I	semi-structured group interviews to evaluate intervention (n = 24, 2 per cluster)	▪ Adoption model [49]	▪ Content analysis [50]	
Response of cluster (intervention)	4. How was the intervention adopted by each nursing home (cluster)?	G	semi-structured telephone interviews to evaluate case conferences (n = 96/6 per nursing team)	▪ Adoption model [49]	▪ Content analysis [50]	▪ DNA double helix
						▪ Blending
						▪ Transformation
		I	semi-structured group interviews to evaluate case conferences (n = 24/1 per team)	▪ Adoption model [49]	▪ Content analysis [50]	
		J	semi-structured group interview to evaluate case conferences (n = 12/1 per cluster)	▪ Adoption model [49]	▪ Content analysis [50]	
		H	semi-structured group interview to evaluate case conferences (n = 12/1 per cluster)	▪ Adoption model [49]	▪ Content analysis [50]	
Recruitment of cluster (intervention)	5. How were the nursing homes (clusters) sampled and recruited for the FallDem study?	N	written documentation of recruitment procedure	-	-	-
	6. Why have the nursing homes participated (or not) in the FallDem study?	K	semi-structured telephone interviews to assess ‘care as usual’ (n = 24/1 per team)	-	▪ Content analysis [50]	▪ DNA double helix
		I	semi-structured group interviews (n = 24/1 per team)	-	▪ Content analysis [50]	
		J	semi-structured group interviews (n = 12/1 per cluster)	-	▪ Content analysis [50]	
Recruitment and reach of individuals (intervention)	7. How were the participants of the intervention recruited by the cluster, and who in the target population actually received the intervention?	A	attendance lists of in-service training in performing case conferences (I), training on the job (II) and case conferences without support (III)	▪ Case conference model (key characteristics)	▪ Descriptive statistics [45]	▪ DNA double helix
		J	semi-structured group interview (n = 12)	-	▪ Content analysis [50]	
		H	semi-structured group interview (n = 12)	-	▪ Content analysis [50]	
Context (intervention)	8. What is the context in which the intervention is being implemented?	K	semi-structured telephone interviews to assess ‘care as usual’ (n = 24)	▪ Case conference model (process structure and key characteristics)	▪ Content analysis [50]	▪ DNA double helix
		L	Dementia milieu assessment (DMA)	-		
		M	standardized questionnaire to assess organizational and structural characteristics of nursing homes/nursing wards	▪ Consolidated Framework for Implementation Research (CFIR) [51, 52]	▪ Descriptive statistics [45]	
	9. What contextual factors promote or inhibit the implementation of the intervention?	A-M	All data assessed throughout the evaluation process	▪ CFIR [51, 52]	▪ Content analysis [50]	▪ DNA double helix

**Table 7 Tab7:** **Data analysis of domains of implementation strategy**

Domain	Research question	Data source		Theoretical basis	Method of data analysis	Method of data integration
Delivery of clusters (implementation strategy)	10. Was the implementation strategy delivered as intended for each nursing home (cluster)?	A	attendance lists of in-service training (3a, b) and steering group meetings (4)	-	▪ Descriptive statistics [45]	▪ DNA double helix
		C	written documentation of in-service training (3a, b) and steering group meetings (4) (deviation from curriculum)	▪ Curriculum (in-service training in dementia and moderator skills (3a, b) and establishment of steering group )	▪ Documentary analysis [46]	
Response of individuals (implementation strategy)	11. What is the attitude of the target population toward the implementation strategy?	F	standardized questionnaire to evaluate in-service trainings (3a, b) and steering group meetings (4)	-	▪ Descriptive statistics [45]	▪ DNA double helix
		G	semi-structured telephone interviews to evaluate implementation strategy (n = 96/4 per nursing ward)	▪ Adoption model [49]	▪ Content analysis [50]	
		I	semi-structured group interviews to evaluate case conferences (n = 24/1 per team)	▪ Adoption model [49]	▪ Content analysis [50]	
		J	semi-structured group interviews to evaluate case conferences (n = 12/1 per cluster)	▪ Adoption model [49]	▪ Content analysis [50]	
		H	semi-structured group interview to evaluate case conferences (n = 12/1 per cluster)	▪ Adoption model [49]	▪ Content analysis [50]	
Response of cluster (implementation strategy)	12. How was the implementation strategy adopted by each cluster?	G	semi-structured telephone interviews to evaluate implementation strategy (n = 96/4 per nursing ward)	▪ Adoption model [49]	▪ Content analysis [50]	▪ DNA double helix
		I	semi-structured group interviews to evaluate case conferences (n = 24/1 per team)	▪ Adoption model [49]	▪ Content analysis [50]	
		J	semi-structured group interview to evaluate case conferences (n = 12/1 per cluster)	▪ Adoption model [49]	▪ Content analysis [50]	
		H	semi-structured group interview to evaluate case conferences (n = 12/1 per cluster)	▪ Adoption model [49]	▪ Content analysis [50]	
Recruitment of individuals (implementation strategy)	13. How were participants of the implementation strategy (IS) recruited by the nursing homes, and who in the target population actually received the IS?	A	attendance lists of in-service training (3a, b) and steering group meetings (4)	-	▪ Descriptive statistics [45]	▪ DNA double helix
		H	semi-structured group interview (n = 12)	-	▪ Content analysis [50]	

All quantitative data (standardized questionnaire) will be analyzed using descriptive statistics [45]. All qualitative data will be analyzed using content analysis [50, 53], a documentary method [48, 54, 55] or document analysis [46].

The semi-structured telephone and group interviews will be primarily deductively assessed using the content analysis technique of Mayring [50, 53]. The application of the deductive category employs previously formulated, theoretically derived aspects of an analysis (see Tables 6 and 7; theoretical basis) and connects these aspects with the text. In a methodological, controlled assignment, a passage of text is linked with a category. Each deductive category has an explicit definition, example and coding rule with regard to the theory and material and is revised during the analysis [50, 53].

The audiotapes of the dementia-specific case conferences will be analyzed using the documentary method [48, 54, 55], which is a reconstructive analysis tool that allows for case comparisons (key concept). Thus, internal and cross-case comparisons as well as the determination of the comparative knowledge of an interviewer will be possible. Four phases will be implemented as follows: (1) the formation of an outline and detailed paraphrasing that begins prior to transcription with a focus on ‘what is said’. To avoid bias, the whole case conference will be transcribed; (2) reflection on interpretation, examining the reconstruction and explication of the orientation frame with a focus on ‘how it is said’ (during phase 2, internal and cross-case comparisons will be initiated to ensure inter-subjectivity of the results); and (3) the ‘stage of case description’ (case structure) phase, during which the essential reconstructed elements will be summarized. For phase 1 (what is said), the ‘act for team model’ will be used [47]. The standardized protocols for the dementia-specific case conferences and the written documentation will be analyzed using documentary analysis [46] (see Tables 6 and 7).

#### Defining delayed treatment effect

It can be assumed that a dementia-specific case conference shows its full treatment effect (100%) when it is delivered over time as intended, is accepted by the nursing team and is adopted by the nursing home. The earliest time point at which a full effect could be expected according to the data is at the transition from training on the job (II) to case conferences without support (III). However, case conferences represent complex interventions that require training and education (as expected, the staff may need more time to learn how to use the case conferences in their daily work routines). Therefore, a delayed treatment effect cannot be excluded (for example, the intervention being only 75% effective after transition from training on the job (II) to case conferences without support (III)). This information provided by the process evaluation will be important for improving model building using a generalized linear mixed-effects model of the effectiveness study. The delay must be modeled as a fractional treatment effect in the mixed-effects model as described by Hussey and Hughes [21]. To define a possible delayed treatment effect for each nursing home, the data pertaining to the delivery of intervention to clusters, the response of individuals to the intervention and the response of clusters to the intervention will be used.

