## Methods/Design

### Study design

The process evaluation is a mixed-method study comprising longitudinal elements, for which quantitative and qualitative data are gathered (Tables 3 and 4). This method will be carried out alongside the FallDem study [13]) between September 2013 and March 2015. A total of 12 nursing homes (clusters) located in the area of North-Rhine-Westphalia (Germany) will take part in the process evaluation. The inclusion criteria for the clusters have been previously published elsewhere [13].

In the FallDem study, the intervention is rolled out every three months to two nursing homes (cluster group) over a period of 18 months (stepped-wedge design). Within every cluster, two nursing wards, which each include one nursing team (core team), participate in the intervention. The order in which the 12 nursing homes will receive the intervention and the type of intervention are determined at random (six WELCOME-IdA clusters and six WELCOME-NEO clusters). Two nursing teams that belong to one cluster will receive the same type of intervention to avoid contamination between WELCOME-IdA and WELCOME-NEO. The last group of clusters includes four instead of two clusters because two nursing homes functioning as cluster reserves will be dropped before the end of the study (Figure 2).

The intervention phase (in-service training during case conferences, on-the-job training and case conferences with support) for each cluster lasts seven months, after which a follow-up phase, which lasts until the end of the data collection period for all 12 clusters (T6), occurs. Hence, the intervention phase is the same duration for each nursing home, but the durations of the pre-intervention and follow-up phases differ (Figure 2).

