**Table 5 Tab5:** **Process structure and key characteristics of both dementia-specific case conferences**

	WELCOME-IdA	WELCOME-NEO
Process structure	Preparation of case conferences (CCs)	
	Introduction (welcome, time frame and roles)	
	▪ Description/quantification of challenging behavior on the basis of IdA (14 guiding questions)	▪ Description/quantification of challenging behavior without assessment (narrative)
	▪ Analyses of triggers and causes of challenging behavior on the basis of IdA (48 guiding questions)	▪ Analyses of triggers and causes of challenging behavior without assessment (narrative)
	Planning of care intervention based on analysis of situation	
	Closing (for example, personal reflection, what have I learned from the case?)	
	Post-processing of case conference (for example, responsibility to transfer results to daily care routines)	
	Evaluation of case conference (for example, changes in challenging behavior due to care interventions and adoption of care interventions)	
	WELCOME-IdA and WELCOME-NEO	
Key characteristics	Participants (core team)	
	1 moderator	
	1 keeper of minutes	
	1 case reporter	
	2 to 5 reflection partners	
	Location	
	undisturbed room/area	
	Duration	
	60 to 90 minutes	
	Intervals	
	(at least) monthly	

WELCOME-NEO is a dementia-specific case conference that supports an open-thinking method. Therefore, it requires that the description and analysis of a challenging behavior be provided in a narrative manner, instead of relying on an assessment instrument for its description and quantification, as well as the determination of its potential triggers and causes (Table 5). Both types of dementia-specific case conferences have predefined process structures and key characteristics that are shown in Table 5.

The interventions of these two dementia-specific case conferences will begin with training in the respective model (WELCOME-IdA or WELCOME-NEO) and will be followed by four supported case conferences (on-the-job training). Then, a minimum of four dementia-specific case conferences will be performed without any assistance (case conferences without support) by the nursing teams (Table 1).

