#### Response of cluster to intervention

For the response of the clusters toward the intervention, four semi-structured telephone interviews [37] will be conducted with the head nurses of each participating nursing ward during the intervention phase. The head nurse should take part in the dementia-specific case conferences (data source G). The goal of the interviews with the head nurse will be to assess whether the structured preparation and post-processing of the dementia-specific case conferences have taken place and whether any changes have occurred due to their implementation. Finally, semi-structured group interviews [38] will be conducted with the steering group, moderators and nursing teams (core teams) at the end of the intervention phase to gain perspective about the overall response of the cluster toward the intervention (data sources H, I and J).

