The limitations of the process evaluation of the FallDem study are also worth noting. The maintenance of dementia-specific case conferences in nursing is an important issue to be explored in a process evaluation; this issue will be only partially addressed in this study. The manner by which individuals and organizations respond to and adopt an intervention may change over time [16], thus, although that topic is beyond the scope of the present study, it may be interesting to determine what will happen during the follow-up-period after the intervention phase of the FallDem study.

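### The fractional treatment variable for the effectiveness model is set home by home from post-randomisation implementation data, so its coefficient is no longer protected by the randomised order of roll-out

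*Protocol article*

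**What the plan says.** Under Study design, randomisation fixes two things: "The order in which the 12 nursing homes will receive the intervention and the type of intervention are determined at random". Roll-out follows a calendar: "the intervention is rolled out every three months to two nursing homes (cluster group) over a period of 18 months".

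The subsection Defining delayed treatment effect then says how treatment is to enter the effectiveness model: "The delay must be modeled as a fractional treatment effect in the mixed-effects model". The fraction is set at the level of the home: "To define a possible delayed treatment effect for each nursing home, the data pertaining to the delivery of intervention to clusters" are used along with the responses of individuals and of clusters. The only partial value given as an example is 75%. The Data analysis section repeats the intention: "a new variable (time combined with the success of the implementation) will be integrated in the generalized linear mixed-effects model". There the variable is built by turning qualitative codes on implementation success into numbers for each cluster. Table 6 lists blending and transformation for research questions 1, 3 and 4, which draw on sources A, B, C and E to J.

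On the inputs, the head-nurse interviews (source G) ask, among other things, "whether any changes have occurred due to their implementation". The group interviews (H, I, J) take place at the end of each home's intervention phase. The description of content analysis after Table 7 says that each deductive category, with its definition and coding rule, is revised as the analysis proceeds.

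**The concern.** In a stepped-wedge trial, the causal claim rests on the crossover time having been drawn at random. A 0/1 indicator of having crossed over is a function of that draw and nothing else. So is a lag curve that is the same for every home. A fraction judged separately for each home is not. It depends on how well the home delivered, accepted and adopted the conferences, all of which is observed after randomisation.

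Two routes can tie that fraction to the outcome. First, a home with better management or staffing may implement better and also improve for reasons unrelated to the conferences. Second, some inputs are collected from staff who have already seen how their residents fared, and the coding rules are not frozen before analysis. By either route, homes that happened to improve tend to receive the larger fractions, and the coefficient drifts towards benefit.

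A third consequence needs no link to outcome. The coefficient becomes the effect projected to a home coded as fully implemented. That is a different quantity from the effect of rolling the conferences out at random.

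**Working it through.** The article gives no alpha, effect size, intracluster correlation or number of residents, so there is no stated figure to reproduce. The following is an illustration, with its assumptions marked.

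**Layout from the article.** 18 months / 3 months = 6 steps; 6 × 2 homes = 12 homes; seven measurement points, T0 to T6. The article also says that the last group has four homes because two are reserves. The figure showing this is not available, so the simple layout of two homes per step is used.

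**Models compared**, for home i at time t, with X = 1 after crossover:
- randomised coding: Y_it = a_i + b_t + θ·X_it + e_it
- home-specific coding: Y_it = a_i + b_t + θ·f_i·X_it + e_it

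**Assumptions.**
- Cluster-period means have independent residuals with SD 1.
- Home and period effects are fixed, and the test is two-sided at 5%.
- Each f_i is constant over time.
- f_i is assigned by rank of a score s_i = ρ·z_i + √(1 − ρ²)·u_i. Here z_i is the home's own standardised observed improvement and u_i is independent noise. ρ stands for whatever correlation arises, by either route.
- There are 4,000 runs per setting, so the Monte Carlo standard error at 5% is √(0.05 × 0.95 / 4000) = 0.003.

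**Result with a true effect of zero** (bias in residual SD units, negative = towards benefit; type I error after the slash):

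| Fractions | ρ = 0 | ρ = 0.3 | ρ = 0.5 | ρ = 0.8 |
|---|---|---|---|---|
| 0.75, 1 | 0.00 / 0.051 | −0.06 / 0.053 | −0.10 / 0.056 | −0.18 / 0.070 |
| 0.5, 0.75, 1 | 0.00 / 0.053 | −0.16 / 0.058 | −0.26 / 0.080 | −0.42 / 0.128 |
| 0.25, 0.5, 0.75, 1 | 0.00 / 0.055 | −0.27 / 0.078 | −0.42 / 0.126 | −0.67 / 0.231 |

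The randomised 0/1 coding gave a type I error of 0.048–0.054 and a bias within ±0.02 in every setting.

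**Result with a uniform true effect of −1 and coding unrelated to outcome (ρ = 0).** The 0/1 model returns −1.00. The home-specific model returns −1.14 with fractions 0.5–1 and −1.11 with fractions 0.25–1. The reported effect is thus 11–14% larger although every home had the same true change.

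**The case against.** The strongest reply is that this article describes the process evaluation only. The effectiveness model belongs to the main trial protocol, which is not shown and may keep an analysis by randomised crossover time as primary. The Background says only that the information can help in designing the model, and the delay is called possible. That stands as a limit: it cannot be concluded that the 0/1 analysis has been abandoned. It does not remove the point, because this article says that the delay must be modelled as a fraction and defines it per home. That is a stated rule, not a detail left to another document.

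A reader might also infer that perceived change in residents' behaviour sets the fraction. The conference structure in Table 5 does include this step: "Evaluation of case conference (for example, changes in challenging behavior due to care interventions and adoption of care interventions"). But the conference protocols (source B) are described and analysed for process structure and key characteristics, source G names neither residents nor behaviour, and the interviews used are coded against an adoption model. No passage says that the evaluated behaviour change feeds the fraction. The risk is open, not documented.

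Two further inferences are not supported. One is that the coding distorts the comparison of WELCOME-IdA with WELCOME-NEO: the article defines no fraction by type and no such contrast for the effectiveness model. The other is that a known share of follow-up measurements would have no implementation data behind it: that count needs a timeline whose figure is not shown and changes if the reserve homes are dropped.

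Finally, rescaling as such is not the fault. A common fraction of 75% also multiplies the same change by 1/0.75 = 1.33. The fault lies in setting the fraction home by home after the fact.

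**Conclusion.** The point holds in this form: the article prescribes, for the effectiveness model, a home-specific treatment variable built from post-randomisation data under coding rules that remain open to revision. Its coefficient does not have the protection of the randomised roll-out order and answers a different question from the effect of roll-out.

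How much this distorts the result cannot be read from the documents. If fraction and outcome are uncorrelated, type I error is kept and only the estimated quantity changes. With fractions of 0.75 and 1, the error is about 5–7%. With fractions from 0.5 to 1 and correlations of 0.5–0.8, it is about 8–13%; a wider spread of fractions gives more. Correlation, spread, residual structure and layout are all assumptions. The figures show direction and plausible range and do not predict this trial's error rate.

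**What to change.** State that the primary effectiveness model codes treatment by the randomised crossover schedule. This can be 0/1, or one fraction by time since crossover that is fixed in advance and common to all homes and both intervention types. A delayed effect can still be modelled in this way.

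Keep the home-specific implementation variable for a model labelled exploratory. For that model:
- fix in advance the rule that turns process data into fractions;
- have the fractions coded and locked by people without access to resident outcomes;
- leave out any item on perceived change in residents.

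If the main trial protocol already makes the randomised-schedule analysis primary, a sentence here saying so settles the first part.

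The cost is wording, a coding rule and a lock date. The small downside is some loss of power if the true delay differs from the common schedule.
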